### Time 2 Assessment

Study staff members will conduct Time 2 (T2) assessments by telephone between 32-36 weeks gestation to re-assess knowledge, contraceptive method selected, and decisional conflict closer to delivery and after the Medicaid sterilization consent form is typically signed. T2 follow-up contact will not exceed 4 weeks from the date of the first contact attempt. A maximum of 5 messages will be left on voicemail (2 during the first week of follow-up and one per week for remaining weeks), unless contact is established with the participant and call backs are requested. The same procedure should be followed for email. The research team will attempt to reach participant for T3 even if they did not complete T2, as long as they did not explicitly withdraw from the study.

### Time 3 Assessment

The final Time 3 (T3) assessment will also be conducted via telephone 3 months postpartum to determine which method, if any, women are actually using and satisfaction with their decision. T3 follow-up contact will not exceed 4 weeks from the date of the first contact attempt and follows the same standards for maximum attempts of contact as T2. As the 3-month follow-up is likely too proximal to experience regret for sterilization decisions, we will focus on other widely-used constructs (decisional conflict and satisfaction with decision) that are strongly correlated with decisional regret.

For those participants whose pregnancy ends before T2 due to miscarriage, termination, or stillbirth, the research team will only proceed with T3 if the participant wishes to continue with their participation. If the participant agrees to be contacted for a T3 interview, T3 follow-up contact will begin at least 3 months after the date the pregnancy ended.

**Figure: Schematic representation of study**

[figure not shown]

## Withdrawal/Lost to Follow Up

### Withdrawal

A participant may withdraw from the study at any time and for any reason. They simply have to communicate to the research staff that they no longer wish to participate in the study.

### Lost to Follow Up

Participants can be deemed lost to follow-up in two scenarios:

1. Once a participant has signed the consent form during their T1 appointment, they are considered “Enrolled” in this study. If a participant has been enrolled but does not complete their T1 appointment during a single session, we refer to these cases as “partial T1s.” If a partial T1 is unable to be rescheduled to complete their interview and if they do not respond to contact attempts made by research staff, they may be classified as Lost to Follow Up. [Contact attempts should be conducted according to outlined follow-up procedures above. Contact attempts may cease after 4 weeks have elapsed from missed appointment with no response from participant OR if increased gestational age would place participant outside of eligibility window for T1.]
2. If the research team is unable to reach a participant at **Time 3** after follow up protocols are followed as specified, participant may be deemed Lost to Follow Up.

**NOTE:** If a participant is unable to be reached at Time 2, they are not considered lost to follow-up and the research team should attempt to reach them again at T3. For these cases, Research staff should have this documented in their records, and then follow up procedures for T3 should be followed as specified above.

## Participant Reimbursement

Participants will be reimbursed up to \$90 for time dedicated to participating in the study. The breakdown for payments is \$40 for T1, \$20 for T2, and \$30 for T3. We have considered both the time it takes to complete each study visit as well as appropriately incentivizing longevity for retention purposes. Pittsburgh and Tennessee will utilize a payment system that provides reloadable debit/Mastercards for participants. These cards will be provided either in-person or mailed once T1 is completed. Once participants have possession of the card, all payments for study assessments can be made remotely. Sites in San Francisco will utilize gift cards that can be mailed, emailed, or sent via text to participants at the completion of each study time point.

## Sample Size Calculation

We based our sample size on the standardized mean differences (Cohen’s d) for the co-primary outcomes of knowledge (0.46) and decisional conflict (0.36) reported in the 2014 Cochrane review of decision aid RCTs. Assuming two-sided alpha levels of 0.025 (for each co-primary outcome) and 15% attrition, 175 women per arm afforded us 80% power to detect these differences.

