## Randomization

Randomization is stratified by site and occurs at the patient level to allocate participants to each of the 2 study arms in a 1:1 ratio, using permuted block randomization that is integrated into the web-based data collection system.

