## Study Arms

### Usual care arm

Our control condition is usual care. Usual care sterilization counseling is likely quite variable, but one consistency is that for women requesting a Medicaid-funded postpartum sterilization, providers must ensure that the standardized Medicaid consent form is signed at least 30 days but no more than 180 days prior to delivery. Consequently, most providers complete the Medicaid sterilization consent form with their patients between 24-32 weeks gestation. This process typically includes counseling on all forms of contraception.

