## Intervention and Timepoints

### Baseline, Intervention, and Time 1 Assessment

Immediately (when possible) after consent, study staff will conduct baseline interviews to assess patient demographic characteristics as well as medical and reproductive history. All assessments will be administered as interviews by study staff who enter the data into REDCap. Women will then be randomized to one of the 2 study arms using computer-generated allocation that is incorporated into the study database. Those randomized to the control (usual care) condition will immediately complete their Time 1 assessment (in person or via phone) to assess knowledge, contraceptive method selected, and decisional conflict. After the baseline survey, those randomized to the intervention arm immediately will use the decision aid on a phone, tablet, or computer. Participants randomized to the decision aid will receive a summary sheet (via email or printout) of their responses, which they are encouraged to share with their healthcare provider. Study staff members will be available throughout to assist participants as needed to answer questions. Following completion of the intervention, staff will then conduct the T1 assessment with the participants. Study procedures at this initial time point will take a total of 60-90 minutes for women in the intervention group and 30-45 minutes for those in the usual care arm.

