## Variables

| Variable                                                                                                                                                                                                                                          | BL | T1 | T2 | T3 |
|---------------------------------------------------------------------------------------------------------------------------------------------------------------------------------------------------------------------------------------------------|----|----|----|----|
| Primary Outcomes                                                                                                                                                                                                                           |    |    |    |    |
| Participant knowledge about tubal sterilization                                                                                                                                                                                                   |    | X  | X  |    |
| Participant decisional conflict in postpartum contraceptive choice                                                                                                                                                                                |    | X  | X  |    |
| Secondary Outcomes                                                                                                                                                                                                                         |    |    |    |    |
| Contraceptive method selected                                                                                                                                                                                                                     |    | X  | X  |    |
| Participant satisfaction with contraceptive decision making                                                                                                                                                                                       |    |    |    | X  |
| Exploratory Outcomes                                                                                                                                                                                                                       |    |    |    |    |

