### Primary and Secondary Hypotheses

For the following primary and secondary hypotheses, we will conduct an intention-to-treat analysis using linear or logistic regression to test intervention effects controlling for study site. The beta coefficient and corresponding 97.5% confidence interval will be used to assess the effect of the intervention.

- **Primary Hypothesis a:** Compared to women who receive usual care alone, women randomized to the decision aid arm will have greater knowledge about sterilization and alternative options at T1
- **Primary Hypothesis b:** Compared to women who receive usual care alone, women randomized to the decision aid arm will have lower decisional conflict in postpartum contraceptive choice at T1
- **Secondary Hypothesis a:** Compared to women who receive usual care alone, women randomized to the decision aid arm will also be less likely to select sterilization and more likely to select an alternative method at T1
- **Secondary Hypothesis b:** Compared to women who receive usual care alone, women randomized to the decision aid arm will also be more satisfied with their decision at 3-month follow-up (T3)

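### A Holm step-down for the two T1 co-primary outcomes would recover about 6 points of power for decisional conflict that the valid, fixed 0.025 split gives up

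*Combined protocol and SAP*

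**What the plan says.** Sample Size Calculation gives standardized differences of 0.46 for knowledge and 0.36 for decisional conflict. It continues "Assuming two-sided alpha levels of 0.025 (for each co-primary outcome) and 15% attrition", and concludes that "175 women per arm afforded us 80% power to detect these differences". Randomization allocates women "to each of the 2 study arms in a 1:1 ratio".

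Primary and Secondary Hypotheses carries the same split into the analysis: "The beta coefficient and corresponding 97.5% confidence interval will be used to assess the effect of the intervention". Both primary hypotheses are set at T1. No step-down, gatekeeping or recycling of alpha is described.

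On timing, women in the control arm "will immediately complete their Time 1 assessment" once randomized, before 24 weeks. The Usual care arm section says that "most providers complete the Medicaid sterilization consent form with their patients between 24-32 weeks gestation". T2 falls at 32-36 weeks. The Primary Outcome Variables table fixes both co-primaries at T1, and the Exploratory Outcome Measures table holds their T2 versions. The summary table under Variables, however, marks T1 and T2 for the row "Participant decisional conflict in postpartum contraceptive choice", and likewise for knowledge, under its primary heading.

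**The concern.** Under a fixed split, decisional conflict is held to 0.025 even after knowledge has been shown. Decisional conflict has the smaller assumed effect, so it sets the sample size and bears most of the cost. Knowledge has about 96% power at 0.025 under the planning assumptions, so its share of alpha would usually be available to pass on. The primary hypothesis names both outcomes, and under the fixed split the chance of showing both is below 80%. At stake is avoidable loss of power, not control of false positives.

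**Working it through.** **Inputs.** From Sample Size Calculation: d = 0.46 and 0.36 (SD = 1), two-sided 0.025 each, 15% attrition, 175 per arm. From Randomization: 1:1. The documents give no correlation between the two test statistics, so I assume 0 to 0.5.

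**Reproducing the plan's figure.** For decisional conflict, n per arm = 2(z₀.₉₈₇₅ + z₀.₈₀)²/d² = 2(2.2414 + 0.8416)²/0.36² = 146.7, so 147. The t-based value is 148, and 148/0.85 = 174.1, so 175. The plan reproduces. Analysed per arm after attrition: 175 × 0.85 = 148.75.

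**Power of each test at 148.75 per arm.** The expected z is d√(n/2).
- Decisional conflict: 0.36 × √74.375 = 3.105. Power is Φ(3.105 − 2.241) = 0.806 at 0.025, and Φ(3.105 − 1.960) = 0.874 at 0.05. The noncentral t gives 0.802 at 0.025.
- Knowledge: 0.46 × √74.375 = 3.967. Power is 0.958 at 0.025 and 0.978 at 0.05.

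**Familywise error.** The fixed split has at most 0.025 + 0.025 = 0.05, or 1 − 0.975² = 0.0494 if the tests are independent. Holm tests the smaller p against 0.025 and, if that is rejected, the other against 0.05. If both nulls are true, a false rejection needs at least one p at or below 0.025, so the bound is again 0.05. If one null is true, its p never faces a level above 0.05. The 5% level therefore holds under any correlation.

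**Holm by hand, correlation 0.**
- Decisional conflict: 0.806 + 0.958 × (0.874 − 0.806) = 0.871.
- Both, fixed split: 0.958 × 0.806 = 0.772.
- Both, Holm: both tests pass 0.05 and at least one passes 0.025. This is 0.978 × 0.874 − (0.978 − 0.958)(0.874 − 0.806) = 0.853.
- At least one: 1 − (1 − 0.958)(1 − 0.806) = 0.992 under either rule, because Holm's first step is the fixed split.

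**Simulation** (2 million draws of two correlated normal statistics; fixed split → Holm):

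| Analysed per arm | Correlation | Knowledge | Decisional conflict | Both | At least one (same for both rules) |
|---|---|---|---|---|---|
| 148.75 | 0 | 95.8% → 97.4% | 80.7% → 87.1% | 77.3% → 85.3% | 99.2% |
| 148.75 | 0.5 | 95.8% → 96.7% | 80.6% → 86.9% | 78.9% → 86.1% | 97.5% |
| 175 | 0 | 98.1% → 98.9% | 87.0% → 92.0% | 85.3% → 91.1% | 99.7% |
| 175 | 0.5 | 98.0% → 98.6% | 87.0% → 91.8% | 86.1% → 91.4% | 99.0% |

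The 175 rows matter because T1 is normally completed in the same session as randomization, so the 15% allowance may be largely unused at T1.

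**Where test and interval part.** Holm gains exactly when one outcome passes 0.025 and the other has p between 0.025 and 0.05. The second outcome's 97.5% interval then includes zero although Holm rejects. At 148.75 per arm this happens in about 6 trials in 100 for decisional conflict and 1 to 2 in 100 for knowledge.

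**The case against.** The fixed split is a legitimate choice. It controls familywise error, it is what the trial was sized for, it delivers the stated 80% per outcome, and test and interval always agree. The documents do not say that both outcomes must succeed, and Holm leaves the chance of at least one success where it was. If nearly all women are analysed at T1, decisional conflict already has about 87% power. All of this stands. It makes Holm an efficiency gain, not the correction of an error.

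The release of alpha from knowledge also depends on d = 0.46, a planning value from an outside review. If the knowledge effect is smaller, decisional conflict gains less, but Holm never falls below the fixed split.

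A reader might go further and infer that the trial cannot make a controlled claim about aid plus usual care versus usual care, because T1 precedes counselling and T2 is the only later time point. The documents do not support this. T3 is also later and carries a secondary hypothesis, satisfaction with the decision. Contraceptive and sterilization counselling and signed consent are recorded at baseline, so some women may have been counselled before T1, and no figure gives the share. The 24-32 week window describes when most providers complete the consent form, not when all counselling starts. The outcome tables and the hypotheses consistently make T1 primary and T2 exploratory, as a check on sustained effect. The Variables table reads most naturally as a collection schedule, since it also marks T1 and T2 for contraceptive method selected under the secondary heading.

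**Conclusion.** The point holds as an efficiency improvement. At an unchanged 5% familywise error, Holm adds about 6 points of power for decisional conflict and 7 to 8 points for showing both outcomes at about 149 per arm. At 175 per arm it adds about 5 points for decisional conflict and 5 to 6 for both. These gains assume d = 0.46 and 0.36 and a correlation of 0 to 0.5. The error control needs none of these assumptions.

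It would be wrong to conclude that the split is invalid or that the trial misses its stated power. Nor does T2 have to enter the confirmatory sequence. That would change the outcome hierarchy, the two existing secondary hypotheses would have to be placed in it, and the documents give no T2 effect size with which to judge its power. It is the sponsor's design choice, not a needed correction. What can fairly be said is narrower: T2 is the only scheduled measurement of the two co-primary outcomes after usual-care counselling typically occurs.

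**What to change.** In Primary and Secondary Hypotheses, state that:
- the two T1 co-primaries are tested by Holm at familywise two-sided 5%: the smaller p against 0.025 and, if that is rejected, the other against 0.05;
- 97.5% intervals are still reported for both;
- the Holm decision governs if a second-step result and its 97.5% interval disagree.

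Make the change before outcome data are seen by arm, and record that it was. The text reads as that of a trial already under way, so the timing needs to be documented. No new data or participants are needed. The cost is that a second-step decision no longer maps one-to-one to the 97.5% interval.

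Optional clarification: describe the T1 result as the immediate effect of the aid, usually before the 24-32 week consent process. Label the Variables table so that T2 knowledge and T2 decisional conflict appear as exploratory, in line with the outcome tables and the hypotheses.

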## Data Collection and Management Responsibilities

### Data Management

Research staff are responsible for maintaining the confidentiality of study participants. All of the participant-facing materials will be identified by a unique ID number. All paper study records containing participant identifiers will be stored separately from records identified by the participant’s study ID. Any files linking a participant’s ID number with their name will be stored on each site’s hard drive, which is only accessible through two-factor authentication. All other study data will be collected and managed using REDCap electronic data capture tools hosted by the University of Pittsburgh. REDCap (Research Electronic Data Capture) is a secure, web-based software platform designed to support data capture for research studies, providing 1) an intuitive interface for validated data capture; 2) audit trails for tracking data manipulation and export procedures; 3) automated export procedures for seamless data downloads to common statistical packages; and 4) procedures for data integration and interoperability with external sources.

In addition to the investigators and their research staff, authorized representatives from the University of Pittsburgh Office of Research Protections may review the data solely for the purpose of monitoring the conduct of this study. De-identified data may also be shared with researchers at the University of Pittsburgh; the University of California, San Francisco ; the

University of Tennessee, Knoxville, the National Institutes of Health (NIH); and with our decision aid web development team.

Table: Maintenance and location of data sources

| Data:                                                        | Data Location:                                                                                                                                           | Task:                                                                  | When to Perform Task:      | Notes:                                                                                                                                |
|--------------------------------------------------------------|----------------------------------------------------------------------------------------------------------------------------------------------------------|------------------------------------------------------------------------|----------------------------|---------------------------------------------------------------------------------------------------------------------------------------|
| Clinic patient schedules                                     | EMR database                                                                                                                                             | Review clinic schedules to screen for potentially eligible patients    | Weekly or biweekly         |                                                                                                                                       |
| Patient contact information                                  | EMR database                                                                                                                                             | After applying eligibility criteria, store on REDCap & site hard drive | Each contact with patient  |                                                                                                                                       |
| Consent forms                                                | Verbal Consents are stored in research assistant's laptop. Written Consents are stored in a study binder behind two locks accessible to only study staff | Save or scan and upload to REDCap & site-specific hard drive           | During study enrollment    | Verbal Consents: Provide participant with blank copy (if possible)
Written Consents: Provide copy of signed consent to participant |
| Decision aid user data                                       | WordPress & Google Analytics                                                                                                                             |                                                                        |                            | Only unique user IDs will be stored                                                                                                   |
| Other data (screening, post-intervention, T2 and T3 surveys) | RED Cap                                                                                                                                                  | Log enrollment status, T1-T3 completion dates in site hard drive       | When new data is available | No hardcopies will be produced                                                                                                        |

